### Implementation procedure

The project timelines are illustrated in Fig. 1. Baseline data collection will occur during months 1–3, during which data pertaining to current antimicrobial utilisation and prescribing appropriateness will be captured daily through the CQR, E-CRF and site survey. During this pre-implementation period, the Champions and RAs will undertake online education and receive training from the project team in review processes and orientation to the data in the A&F reports. In parallel, the Champions will engage the wider ICU team to complete the actions described above. Data on existing prescribing practices, which is already captured as part of the CQR report (see Table 1 below) will remain available to the ICUs.

**Fig. 1 Fig1:**
[figure not shown]
Project timeline

At month 4, ICU teams will commence the protocolised review in their ICU. The Champion will have access to the online enhanced CQR reports, and the online education material will remain available to all ICU team members. Online support for troubleshooting relating to the implementation strategies will be available to the Champions. In addition, voluntary monthly group sessions will be facilitated by the project team from months 4–6, whereby Champions, RAs and other team members will be welcome to join to reflect on their experience and share learning between sites. Daily data collection (CQR and E-CRF) will continue throughout this period. Champions will be interviewed during months 4–6 to explore barriers and facilitators to implementation, adaptations made to both the intervention and its implementation, along with perceptions regarding likely adoption and maintenance (Supplementary File 3).

At the end of month 6, the implementation strategies of online education, the role of Champions, and the RA collecting daily data on review processes will cease. The daily auditing of whether reviews take place will be transferred to the CQR data collectors and reported monthly as part of the CQR report. A second interview will be conducted with Champions following month 6 to explore barriers and facilitators to adoption, and adaptations to the intervention made post-implementation (Supplementary File 4).

### Adaptations to implementation plan

It is expected that ICU teams will make adaptations to their prescribing review processes. These adaptations will be captured throughout the project by Champions (in implementation logs) and synthesised by the project team as part of the evaluation. Adaptations may also be made to the implementation strategies, with the proviso that any adaptations are made at a ‘project level’, meaning uniformity of materials and resources across all sites. Site or regional level adaptations to implementation strategies will not be made. For example, the structure and/or content of weekly reports may be adapted, or elements may be added to or removed from the online education resource, following feedback. Such adaptations, and the reasons for them, will be logged, explored during interviews and synthesised.

### Outcomes

#### Primary outcome: implementation

Implementation is the primary outcome and will be assessed quantitatively using 3 of the 5 key domains identified through the RE-AIM framework: Reach, Implementation (defined as fidelity) and Adoption (see Table 1). These will be combined into a composite measure of implementation with a threshold of 80% for success in each domain. Furthermore, Champions’ perceptions of the determinants of successful implementation, including acceptability, maintenance of, and adaptations to, implementation will be captured through field notes and interviews [51].

#### Secondary outcomes: Intervention effectiveness

Intervention effectiveness, defined as the intervention's effect on the relevant care processes and clinical outcomes, will be assessed by reporting ICU trends in *prescription appropriateness* (Antimicrobial density (AD), treatment duration (DOT) and antimicrobial redundancy rate (ARR, % of total prescriptions)), and *processes of care* (proportion of patients for whom cultures are sent, antimicrobial resistance rate, antimicrobial prescribing rate and compliance of prescriptions with local guidelines). Clinical care processes and outcomes (mortality, Length of Stay and duration of organ support) will be also collected as safety endpoints. Unintended and/or adverse consequences of the intervention will also be explored through field notes and interviews with Champions.

#### Feasibility of collecting outcomes

Eligible ICUs will have had a CQR established for at least 6 months and have an established CQR data collector. Clinical teams will already be trained in use of the CQR, and in the review and interpretation of CQR reports which will be used for audit and feedback. ICU team members, including the Champion will work together with the existing CQR and clinical teams to ensure that data on implementation and care processes can be integrated into analysis of outcomes. This will include records that include (1) diagnoses, (2) prescriptions of medications, (3) investigations and observations, and (4) care processes associated with AMS and the preselected outcomes. Information on the 4 steps of review (indication, route, expected duration, and expected stop date) will be recorded, either on paper, or electronically and reported as part of the audit and feedback as described above. CQR reports will be generated centrally by the CCAA data coordinating centre and made available to sites through existing mechanisms. Data pertaining to the availability of the above review and CQR information will be used as part of the implementation evaluation.

### Data collection

Data regarding case mix (including source and reason for admission, severity of illness at admission, comorbidities) along with physiology, organ support, antimicrobial prescriptions and microbiology data, care processes (duration of antimicrobials) and clinical outcomes will continue to be collected daily through the existing CQR during months 1–8. The CQR data collectors will also collect adoption and reach of any pre-existing structured review during months 1–2.

A project specific E-CRF on REDcap [52, 53], will capture data on antimicrobial reviews during months 4–6 (see Table 1 above). This additional E-CRF collection will be done by the RAs. Copies of existing antimicrobial guidelines will be requested prior to commencement of the study, and ICU stakeholders’ perspectives regarding the current guidelines, along with information on existing antimicrobial stewardship activities already present in the ICU captured during the site onboarding by Champions. Changes in guidelines made during the project will also be captured, and the current working version of the guidelines queried at each phase of the project. Post implementation (months 7 onwards), the CQR data collection will continue, along with a measure of adoption.

Qualitative data exploring the Champions’ perspectives regarding implementation, acceptability, adoption and maintenance, along with contextual factors influencing implementation will be collected through semi-structured interviews at two time points during the study: implementation (months 4–6) and post-implementation (month > 6). We intend to interview all Champions during both phases but recruitment may cease if concurrent analysis indicates that theoretical saturation has been achieved. Interviews will be conducted remotely using the Zoom (Zoom Video Communications Inc, San Jose, CA, USA) conferencing application. A participant information sheet (Supplementary File 5) will be provided and verbal consent for participation sought (Supplementary File 6). In addition, Champions together with RAs will be requested to maintain an implementation log [54], whereby adaptations, and observed barriers and facilitators to implementation will also be reported. These will be reviewed and thematically coded alongside the interview data.

No site or follow-up visits by the project team are required, as the design of the project is such that ICU teams together with Champions have direct ownership at site level, and the project seeks to minimise additional burden of data collection for clinical staff. All patient level de-identified data will be submitted by collaborating CQRs using existing processes. All data will be inspected before analysis to rule out spurious values, and appropriate transformations implemented where necessary. Existing data quality measures already operational within the CQRs will be utilised to provide information on data availability and reduce erroneous or missed data. These measures are already described in detail and published [55]. Once cleaned, data will be aggregated and anonymised at ICU level for monthly and weekly reporting (audit and feedback) and for the subsequent project analysi.

### Analysis

All analysis will be conducted at the level of ICUs. ICUs will be identifiable only by their type (i.e. medical, surgical, mixed or speciality), and by their organisation governance type (private, public, other). ICUs who have a pre-existing structured review with an adoption rate of 80% will be included in the context description, but not in the intervention analysis described below. No country or regional level analysis is planned. However participating CQRs will have access to their sites’ data for subsequent evaluation once the primary outcome is published.

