### Recruitment

We anticipate recruiting between 35–40 ICUs. Using existing CQR data from collaborating registries, we estimate that 75% of adult patients admitted to ICUs receive one or more antimicrobials. ICU occupancy varies between ICUs, but we estimate a median admission rate of 40 patients per month. Therefore, we expect a median inclusion of 180 ICU patient encounters for each ICU during the 6-month period, (totalling approximately 6300 ICU encounters).

Interviews with ICU Champions are described below. One interview with each Champion will be conducted during months 4–6, and one following month 6, resulting in 70 interviews (35 ICUs*2) and 3 months of field notes (recorded during months 4–6). Implementation challenges and effectiveness are likely to vary across sites, so we aim to include qualitative data from all sites. Qualitative data may, however, have a lower sample size as we will stop during each round when we reach saturation or predictability (data will be analysed contemporaneously).

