For the secondary outcomes, we will perform an interrupted times series analysis. We will observe the weekly temporal resolution of each indicator and set the model to account for the natural/secular time trend, implementation of the intervention (level change) and the trend after implementation (slope change). We will account for auto-correlations. The model applied will depend on the data, but we will evaluate ARIMA models, segmented regressions and Holt-Winters additive model to evaluate the best model for the times series. Counts of actions recorded in response to the review will be described. The code lists for the primary and the secondary outcomes, and definitions for indicators of quality will be developed and published in advance of data collection.

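### Mortality is a safety endpoint, but the ICU-level aggregation rule drops the patient-level link between severity and death, so a case-mix shift at month 4 could mimic or mask harm

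*Protocol article*

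**What the plan says.** Under Secondary outcomes: Intervention effectiveness, the protocol article states: "Clinical care processes and outcomes (mortality, Length of Stay and duration of organ support) will be also collected as safety endpoints". No comparison, margin or model is given for mortality.

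Two sentences fix the form of the analysis data. The Analysis section says "All analysis will be conducted at the level of ICUs". Data collection says that, after cleaning, "data will be aggregated and anonymised at ICU level for monthly and weekly reporting (audit and feedback) and for the subsequent project" analysis. Neither exempts the safety endpoints.

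For the secondary outcomes, Statistics plans an interrupted time series at weekly resolution. It will "set the model to account for the natural/secular time trend, implementation of the intervention (level change) and the trend after implementation (slope change") and allow for autocorrelation. No case-mix or severity term is named.

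The data for adjustment exist. Data collection lists, among the items captured daily through the registry, "Data regarding case mix (including source and reason for admission, severity of illness at admission, comorbidities"). It also says "All patient level de-identified data will be submitted by collaborating CQRs using existing processes".

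**The concern.** The intervention encourages teams to stop, narrow or avoid antimicrobials in critically ill patients, so the harm to look for is under-treatment, and mortality is the natural place to look. The design has no concurrent control. A change in deaths after month 4 could come from the review or from a change in who was admitted. Trend terms deal with gradual drift. They do not remove a shift in case mix that happens to fall at month 4, because the level-change term absorbs it.

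Severity adjustment is the usual protection, and it works best when each patient's severity is linked to that patient's outcome. The aggregation rule breaks this link before the analysis. At stake is whether the trial can say anything interpretable about mortality in either direction.

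**Working it through.** **1. The plan's own size figure.** Recruitment gives a median of 40 admissions per ICU per month, 75% on antimicrobials, and 35 ICUs. 40 × 0.75 × 6 = 180 encounters per ICU, which matches "we expect a median inclusion of 180 ICU patient encounters for each ICU during the 6-month period". 180 × 35 = 6300, the stated total. The figure reproduces.

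**2. Pooled precision.** Taking the six months as months 1-6, split equally at month 4, gives 90 v 90 encounters per ICU and 90 × 35 = 3150 v 3150 overall. The documents give no mortality rate, so it is assumed. The 95% half-width for a crude difference is 1.96 × √(2p(1−p)/n):

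| Assumed mortality | Half-width, 3150 v 3150 |
|---|---|
| 10% | ±1.5 points |
| 20% | ±2.0 points |
| 25% | ±2.1 points |
| 30% | ±2.3 points |
| 40% | ±2.4 points |

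On all admissions (40 × 3 × 35 = 4200 v 4200), the figure at 25% is ±1.9 points.

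**3. Allowing ICUs to differ in their true change.** Averaging 35 ICU-level changes with an assumed between-ICU SD τ, the half-width is 1.96 × √[(2p(1−p)/90 + τ²)/35]. At p = 25%, 2p(1−p)/90 = 0.00417, so:
- τ = 0: 1.96 × √(0.00417/35) = ±2.1 points
- τ = 5 points: 1.96 × √(0.00667/35) = ±2.7 points
- τ = 10 points: 1.96 × √(0.01417/35) = ±3.9 points

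These are crude comparisons. A secular-trend term would widen them, because trend and step are correlated.

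**4. What a case-mix shift alone can do.** At 25% mortality the odds are 0.25/0.75 = 0.333.
- × 1.15 = 0.383, and 0.383/1.383 = 27.7%, a rise of 2.7 points.
- × 1.25 = 0.417, and 0.417/1.417 = 29.4%, a rise of 4.4 points.

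A second illustration assumes the high-risk share moves from 30% to 40%, with mortality 50% in high-risk and 10% in other patients. The crude rate changes by 0.10 × 0.40 = 4.0 points with no treatment effect. The reverse shift would hide a true rise of 4.0 points.

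**5. Comparison.** Spurious movements of 2.7 to 4.4 points stand against half-widths of about 2 to 4 points. The larger shift exceeds the half-width at every τ shown. The smaller exceeds it at τ = 0, about equals it at τ = 5, and falls below it at τ = 10. So pooling without adjustment does not settle the matter: it narrows the interval and leaves the bias in place.

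**6. Can aggregated severity substitute?** Partly. Mean severity could enter an ICU-level model, but 90/13 is about 7 encounters per ICU per week. A weekly ICU mean on that base is noisy, and relating it to weekly deaths is an ecological adjustment.

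**The case against.** **Per-ICU comparison.** A reader might infer that mortality will be judged one ICU at a time, where 90 v 90 patients at 25% mortality give 1.96 × √(2 × 0.25 × 0.75/90) = ±12.7 points. The text does not support this. The only per-ICU before-after criterion, a 10% absolute reduction, covers redundancy, density and duration of treatment. The primary analysis shows that ICU-level results are combined across ICUs. The contrast between ±12.7 and ±2.1 is √35 ≈ 5.9, which is the effect of pooling. ICU-level analysis can have that gain too, so precision is no argument against it.

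**Denominator.** A reader might also infer that only patients on antimicrobials count towards mortality. The 180 encounters are a recruitment estimate, and no passage makes them the mortality denominator. Under Conduct of review, the review acts on prescriptions already started, so a patient whose drug is stopped has normally already received one.

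**Silence and the analysis plan.** Nothing says mortality will go unadjusted, and covariates for a safety endpoint are often left to an analysis plan. Patient-level data are submitted before aggregation, so risk-standardised rates could be derived first. Limitations already concedes weak causal attribution, and the article nowhere promises a finding of safety.

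**What stands.** The first two points stand in full. The third stands in part: missing detail would not be a finding, but the aggregation rule is stated for all analysis. A patient-level adjusted mortality model in an analysis plan would contradict it, so the protocol wording itself needs the exemption.

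**Conclusion.** The point holds in a limited form. The article confines project analysis to ICU-level aggregates, names no case-mix term, and makes mortality a safety endpoint without exempting it. Followed literally, this leaves an uncontrolled mortality comparison open to a case-mix shift at month 4, while the data that would reduce the problem are already collected. Plausible shifts are of the same order as the whole pooled half-width: 2.7 to 4.4 points against about ±2 to 4.

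The 25% mortality, the odds multipliers, the high-risk shares and the between-ICU SDs are assumptions; the documents give none of them. They show that a shift would matter, not that one is expected. Because mortality is neither the primary outcome nor subject to a stated decision rule, this is an improvement the plan should make rather than a flaw that invalidates the trial.

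**What to change.** Exempt the safety endpoints from the ICU-level rule in Analysis and from the aggregation step in Data collection. Then do one of the following and report the pooled adjusted effect with its 95% CI.

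- **Preferred.** Fit a patient-level mixed logistic model across all participating ICUs and all ICU admissions, with an ICU random intercept, a random period effect and a calendar-time term. Adjust for severity, source and reason for admission, and comorbidities. The calendar-time term keeps the control for secular trend that the plan already uses for the other secondary outcomes; without it the model would be a bare before-after contrast. Stating all admissions as the population also settles a denominator that the article leaves open.
- **Within the ICU-level rule.** Compute risk-standardised (observed/expected) mortality from patient-level data before aggregating, and use it as the series in the time-series model.

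The cost is revised wording, one extra model, keeping the de-identified patient-level file for analysis, and a stated method for missing severity data. Adjustment addresses measured case mix only, so the existing caveat on causal attribution should stay.

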#### Primary outcome

Successful implementation will be assessed by a composite measure combining rates of fidelity, reach, and adoption. Recent literature describes that for a multifaceted intervention to affect clinical practice change, implementation threshold needs to be 80% [58]–[63]. We will therefore consider this as the threshold for successful implementation at ICU level.

#### Secondary outcomes

For the secondary outcomes of intervention effectiveness, we propose a 10% absolute reduction in Antimicrobial Redundancy Rates (ARR) (Supplementary File 8), Antimicrobial Density (AD), and Duration of Treatment (DoT) (independently), compared with the baseline period, for successful intervention at the ICU level.

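### The 10% success rule for each ICU compares with the baseline level, has no uncertainty bound, and is not tied to the interrupted time series planned for the same outcomes

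*Protocol article*

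**What the plan says.** Under Analysis, Secondary outcomes, the protocol article sets the target: "we propose a 10% absolute reduction in Antimicrobial Redundancy Rates (ARR", with AD and DoT held to the same figure and each taken on its own, "compared with the baseline period, for successful intervention at the ICU level". The sentence names no confidence limit, test, minimum denominator, trend adjustment or post-implementation period.

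Under Statistics, the same outcomes are assigned to an interrupted time series on weekly data, with autocorrelation handled and the model set to "account for the natural/secular time trend, implementation of the intervention (level change) and the trend after implementation (slope change".

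Implementation procedure fixes the periods: "Baseline data collection will occur during months 1–3", and "At month 4, ICU teams will commence the protocolised review in their ICU".

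The only figures bearing on precision within an ICU are in Recruitment: "we estimate a median admission rate of 40 patients per month", "we estimate that 75% of adult patients admitted to ICUs receive one or more antimicrobials", and so "we expect a median inclusion of 180 ICU patient encounters for each ICU during the 6-month period". No error rate or power is given for the 10% rule.

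**The concern.** The second objective is to evaluate the effect of the structured review on antimicrobial use, and the 10% rule is the only success criterion stated for it. Two features make it a weak criterion.

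- **Different contrasts.** The rule asks whether the later period is lower than the baseline period. The time series asks whether the later period departs from where the baseline trend was heading. They agree only when there is no trend. The Statistics section accepts that a secular trend has to be accounted for; the rule, followed as written, leaves it in and credits it to the intervention.
- **No allowance for sampling variation.** The rule works at the level of a single ICU, where the expected volume is small. An ICU can cross the line by chance, or miss it despite a real reduction.

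At stake is whether an effectiveness statement for an ICU reflects the intervention, a trend already under way, or noise. The analysis could also return two answers for the same outcome with no stated way to choose between them.

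**Working it through.** **1. The plan's own volumes.** 40 admissions per month × 0.75 × 6 months = 180 encounters per ICU, and 180 × 35 = 6300. Both match Recruitment. Half of 180 gives about 90 treated encounters in months 1-3 and 90 in months 4-6.

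**2. Assumptions where the document is silent.** Baseline ARR 20-50%; one prescription per encounter (two as a variant); independent prescriptions; post period months 4-6 (month 7 alone as a variant). ARR is a percentage of prescriptions, so 10% absolute is read as 10 points.

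**3. Chance of meeting the ARR rule with no effect and no trend.** Exact probability that observed baseline ARR minus observed later ARR is at least 0.10, with both counts binomial at the same true rate:

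| Prescriptions, baseline vs later | ARR 20% | 30% | 40% | 50% |
|---|---|---|---|---|
| 90 vs 90 | 5.6% | 8.3% | 9.8% | 10.3% |
| 180 vs 180 | 1.1% | 2.2% | 3.0% | 3.3% |
| 45 vs 45 (small ICU, or design effect 2) | 11.7% | 15.0% | 16.6% | 17.1% |
| 90 vs 30 (month 7 only) | 13.0% | 16.5% | 18.1% | 18.6% |

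At a baseline ARR of 10% the first two rows fall to 1.7% and 0.1%.

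**4. Precision of one ICU's change.** The 95% half-width is 1.96 × √(2p(1−p)/90).
- p = 0.20: 1.96 × √(0.32/90) = 0.117.
- p = 0.50: 1.96 × √(0.50/90) = 0.146.

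That is 11.7 to 14.6 points, against a threshold of 10.

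**5. Pre-existing decline, no effect (90 vs 90, ARR 20-50%).** The period midpoints are 3 months apart, so a decline of s points per month lowers the later period by 3s.

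| Decline per month | Built-in fall | Chance of meeting the rule |
|---|---|---|
| 1 point | 3 points | 13-19% |
| 2 points | 6 points | 27-32% |
| 3 points | 9 points | 47-48% |

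The reverse also holds. With a prior rise of 1 point per month, a true 10-point fall below the projected trend appears as 10 − 3 = 7 points against baseline, and misses the target.

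**6. A true 10-point fall with no trend** meets the rule 53-54% of the time.

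**7. DoT, under two further assumptions.** Read the 10% as relative and take a coefficient of variation (CV) of 0.8-1.0. The chance of success with no effect is Φ(−0.10 / (CV × √(2/90))).
- CV 0.8: the standard error (SE) is 0.8 × 0.149 = 0.119, giving 20%.
- CV 1.0: SE 0.149, giving 25%.

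**8. What a trend-adjusted estimate can deliver.** Segmented regression on 12 + 12 weeks, with 90/12 = 7.5 encounters per week and ARR 20-50%, gives an SE for the level change of about 12-15 points in a single ICU. Dividing by √35 gives about 2.0-2.5 points pooled. These SEs ignore autocorrelation and between-ICU variation, so they are lower bounds.

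**The case against.** The strongest reply is that the two sections belong together: one states a target size, the other states how change is estimated, and an analysis plan not shown may join them. This stands in part. The text nowhere says that the 10% is an unadjusted difference, so calling the rule a raw before-after comparison is an inference. But the target sentence does fix a comparator, the baseline period, and that is not the contrast the time series estimates. A later plan reading the target from the model would change that comparator as well as fill in detail.

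Four stronger readings are tempting and are not supported:

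- *That ICUs will be declared successes by chance, in large numbers.* The documents support only that they can be. The ARR rate depends on a baseline rate and prescription volume that are not given, and is small at 180 prescriptions per period.
- *That success on any one of the three outcomes is enough.* The protocol judges them independently and has no such combined rule.
- *That a count of successful ICUs would mislead.* A proportion of ICUs reaching a threshold is planned for the primary outcome only.
- *That the DoT figures are as firm as those for ARR.* They replace the stated absolute reduction with a relative one and rest on an assumed CV.

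It is also fair to say that firing about half the time when the truth sits at the cut-off is a property of any point threshold, and that Limitations concedes weak causal attribution. That concession does not repair a success label that leaves the trend in.

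**Conclusion.** The point holds in limited form. The ICU-level rule has no uncertainty bound, no named post period and no stated tie to the interrupted time series, and its comparator can give a different answer from that model whenever a secular trend exists.

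For ARR, the chance of success without effect is about 6-10% at 90 prescriptions per period and about 1-3% at 180. A prior decline of 2-3 points per month raises the figure at 90 prescriptions to about 27-48%. One ICU's change is uncertain by about ±12 to ±15 points. These figures assume a baseline ARR of 20-50%, independent prescriptions and months 4-6 as the post period; the trends are illustrative and not taken from the documents. The DoT figure of 20-25% is conditional on the relative reading and the assumed CV. AD was not quantified, because the document gives no measure of its spread.

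The difference in comparators depends on none of these numbers. It concerns secondary outcomes only; the primary implementation outcome is unaffected.

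**What to change.** In Analysis, Secondary outcomes, state that effectiveness for each of ARR, AD and DoT is judged from the interrupted time series described under Statistics, fitted as one pooled or hierarchical model across ICUs. Name the post period. Estimate the difference from the trend-projected counterfactual over that period with a 95% CI, and report it against the 10% target. Report ICU-level changes descriptively with intervals, and not as success or failure on the baseline comparison alone.

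Two lighter repairs fall short. Also requiring each ICU's 95% CI to exclude zero would lower chance success on ARR to about 2.6-2.8% (90 vs 90, ARR 20-50%, no trend), but it leaves the trend in. A separate time series per ICU removes the trend, but with an SE of about 12-15 points it is too imprecise for a 10-point target.

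The cost is a reworded paragraph and somewhat more modelling of data already being collected; no additional patients or data are needed. The downside is that trend-adjusted intervals are wider than those of a simple before-after difference, and ICUs no longer receive an individual success label.
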